## Abstract

**Background:**

The surgical techniques for treatment of chronic subdural hematoma (CSDH), a common neurosurgical condition, have been discussed in a lot of clinical literature. However, the recurrence proportion after CSDH surgery remains high, ranging from 10 to 20%. The standard surgical procedure for CSDH involves a craniostomy to evacuate the hematoma, but irrigating the hematoma cavity during the procedure is debatable. The authors hypothesized that the choice of irrigation fluid might be a key factor affecting the outcomes of surgery. This multicenter randomized controlled trial aims to investigate whether intraoperative irrigation using artificial cerebrospinal fluid (ACF) followed by the placement of a subdural drain would yield superior results compared to the placement of a subdural drain alone for CSDH.

**Methods:**

The study will be conducted across 19 neurosurgical departments in Japan. The 1186 eligible patients will be randomly allocated to two groups: irrigation using ACF or not. In either group, a subdural drain is to be placed for at least 12 h postoperatively. Similar to what was done in previous studies, we set the proportion of patients that meet the criteria for ipsilateral reoperation at 7% in the irrigation group and 12% in the non-irrigation group. The primary endpoint is the proportion of patients who meet the criteria for ipsilateral reoperation within 6 months of surgery (clinical worsening of symptoms and increased hematoma on imaging compared with the postoperative state). The secondary endpoints are the proportion of reoperations within 6 months, the proportion being stratified by preoperative hematoma architecture by computed tomography (CT) scan, neurological symptoms, patient condition, mortality at 6 months, complications associated with surgery, length of hospital stay from surgery to discharge, and time of the surgical procedure.

**Discussion:**

We present the study protocol for a multicenter randomized controlled trial to investigate our hypothesis that intraoperative irrigation with ACF reduces the recurrence proportion after the removal of chronic subdural hematomas compared with no irrigation.

**Trial registration:**

ClinicalTrials.gov jRCT1041220124. Registered on January 13, 2023.

**Supplementary Information:**

The online version contains supplementary material available at 10.1186/s13063-023-07889-7.

## Introduction

### Background and rationale {6a}

Chronic subdural hematoma (CSDH) is a neurological condition caused by a hematoma that slowly collects in the subdural space between the dura mater and brain. CSDH is one of the most common neurosurgical disorders, particularly in the elderly population [1, 2]. As the world population ages, the incidence and median age of patients with CSDH steadily increase [3, 4]. CSDH presents with a variety of neurological symptoms, ranging from mild symptoms such as headache and dizziness to severe symptoms like disorientation. In cases with minimal or no symptoms, the hematoma may resolve spontaneously, while in severe cases, surgery is indicated when the symptoms progress or the volume of the hematoma is large [5, 6]. Surgical outcomes are generally favorable, but hematoma regrows in 10–20% of cases postoperatively and necessitates reoperation [1]. Therefore, appropriate surgical procedures must be established to reduce postoperative recurrence.

The focus of this study stems from the debate over the efficacy of intraoperative irrigation — a technique involving washing out the hematoma during surgery — in preventing the hematoma recurrence. Some studies suggest that irrigation significantly reduces recurrence rates, while others report no difference or even that perfusion should be avoided [7–16]. A meta-analysis including some of these studies revealed no significant difference in recurrence or complications between the two methods [17]. As a reason for these inconclusive results, variability in the type of irrigation fluid used can be considered. Specifically, in previous studies, artificial cerebrospinal fluid (ACF) (Table 1) was not used when washing out hematomas. Recent reports suggest that ACF is more effective in reducing recurrence rates compared to normal saline [18]. Therefore, a more definitive investigation is needed regarding the role of intraoperative irrigation in the management of CSDH when appropriate perfusion fluids are used.

**Table 1 Tab1:** Composition of human spinal fluid and solutions used in neurosurgery

Component	Normal human CSF	ACF	NS	LR
Na^+^ (mEq/L)	145	145	154	130
K^+^ (mEq/L)	2.8	2.8	0	4
Mg^2+^ (mEq/L)	2.2	2.2	0	0
Ca^2+^ (mEq/L)	2.3	2.3	0	3
Cl^−^ (mEq/L)	111.9	129	154	109
P (mmol/L)	1.1	1.1	0	0
HCO^3−^ (mEq/L)	23.1	23.1	0	0
Lactate^−^ (mEq/L)	0	0	0	28
Glucose (g/L)	0.61	0.61	0	0
Osmolality ratio	≈1	≈1	1	≈0.9
pH	7.307	≈7.3	≈6.3	≈6.7

*Abbreviations*: *CSF* cerebrospinal fluid, *ACF* artificial cerebrospinal fluid, *NS* normal saline, *LR* lactated Ringer’s solution

Furthermore, various factors like age, antithrombotic therapy, alcoholism, and pre- and postoperative computed tomography (CT) have been identified as recurrence risks, underscoring the need for a comprehensive approach to studying CSDH recurrence [19–25].

### Objectives {7}

We hypothesized that with the use of appropriate irrigation fluid, CSDH surgery with irrigation would reduce the recurrence rate compared to the non-irrigation group. The primary objective of this study is to determine whether intraoperative irrigation with ACF or no irrigation is associated with better clinical outcomes and recurrence proportions of CSDH. This will be measured primarily by the rate of meeting criteria for symptomatic CSDH recurrence necessitating reoperation within a 6-month period post-surgery. Furthermore, this study seeks to explore the potential of irrigation as a more effective intervention for patients at high risk of CSDH recurrence, thereby providing a more holistic understanding of the condition's management by stratifying the CSDH patient background.

### Trial design {8}

This study is a prospective, multicenter randomized, controlled, non-blinded trial. This study evaluates intraoperative irrigation via ACF with a subdural drain versus a subdural drain alone after the evacuation of a CSDH. Except for randomization to irrigation versus no irrigation, the management of the study participants will not differ from the current management of patients. A 1:1 stratified randomization will be performed at each site using a web-based system. Clinical symptoms and imaging assessments will be conducted by the treating physicians at each facility, following the timeline of the participants.

### Eligibility criteria {10}

#### Study participants

Patients diagnosed with CSDH for whom surgical resection is indicated will be screened for participation.

#### Inclusion criteria

Patients with symptomatic CSDH requiring burr-hole evacuationPatients > 20 yearsPatients undergoing surgery for single-sided CSDH

#### Exclusion criteria

Patients who have previously undergone a craniotomyPatients who have previously received an ipsilateral craniostomyPatients with spinal fluid shuntingPatients with intracranial mass lesions that may affect their current symptoms (e.g., very small tumors or contralateral hematomas) should be excluded.Patients who have received radiation or chemotherapy within the last 5 yearsImmunocompromised statesPatients with such severe thrombotic risk from the discontinuation of antithrombotic drugs are not tolerated (recent cardiac or intracranial stents, recent pulmonary embolisms, and mechanical valves).Patients deemed unable to insert a drain preoperatively due to a lack of patience or small hematomaPatients who, in the judgment of the investigator, are likely to be non-compliant or uncooperative during the study.

### Who will take informed consent? {26a}

In this study, a neurosurgeon, who is also an investigator or subinvestigator, approaches patients who are eligible for CSDH surgery. Following the explanation and consent for surgery, patients are informed about the study. Patients are enrolled in the study only if they consent to both the surgery and the research. If a patient is unable to provide written consent, it will be obtained from their next of kin. Patients who choose not to participate in the study can still receive the same quality treatment as participants. The participants will be free to withdraw from the study at any time in accordance with the most recent 2013 version of the Declaration of Helsinki.

### Additional consent provisions for collection and use of participant data and biological specimens {26b}

We do not currently plan to use samples or information obtained from participants in this research for future studies. If this changes, we will obtain proper ethical approval, document the details clearly, and either secure consent from the participants or provide an opportunity to opt out by making the research information public before using the information in new research.

## Interventions

### Explanation for the choice of comparators {6b}

To evaluate the effectiveness of irrigation using an ACF following the removal of a CSDH, the intervention is to be divided into two groups: one that will undergo hematoma irrigation and another that will not. The most widely and commercially available ACF for neurosurgical procedures in Japan (ARTCEREB Cerebrospinal Surgery Perfusion and Irrigation Solution®, Otsuka Pharmaceutical Factory, Tokushima, Japan) is chosen as the irrigation fluid in this study. Except for washing out the hematoma intraoperatively, all perioperative management will be performed identically across both groups.

### Intervention description {11a}

In the hematoma irrigation group, the subdural space will be irrigated repeatedly until fluid drainage becomes clear, using at least 200 mL of ACF after CSDH removal. A closed drain will then be inserted and left in the cavity for at least 12-h post-surgery.

In contrast, in the non-irrigation group, a drain will be placed without irrigation after performing the burr-hole craniostomy. Similar to the hematoma irrigation group, a closed drain will be left in the cavity for at least 12-h post-surgery.

Previous literature has examined the direction and duration of subdural space drainage, yet a consensus on evidence-based guidelines remains elusive [26–28]. Therefore, this study advocates that the minimum duration of subdural drainage should be at least 12 h, and that the exact position and duration of the drain should be left to the discretion of the attending physician. Similarly, as the optimal volume for irrigation is not yet known [29], the practical volume used in this study is also left to the discretion of the attending physician, with a minimum volume of 200 ml. This approach highlights the importance of clinical judgment in the absence of conclusive evidence and ensures flexibility in patient care while adhering to minimum standards.

### Criteria for discontinuing or modifying allocated interventions {11b}

After randomization, patients who wish to change their assigned surgical procedure can request an intervention change and withdraw from the trial. Patients do not have to provide the reason for withdrawal. If the surgeon intentionally or unintentionally administers a treatment different from the assigned group after randomization, the case will be excluded from the analysis, and crossover of participants is not permitted. This approach ensures the integrity of the trial and respects patient autonomy.

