### Concealment mechanism {16b}

Clinical information required for the minimization method would be inserted into a web-based registration system for allocation. This process will be performed before surgery, and no registrations will be accepted thereafter.

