## Assignment of interventions: blinding

### Who will be blinded {17a}

Given the nature of surgical intervention, it is impossible to blind the medical staff involved. Furthermore, since the primary outcome measure is meeting the criteria for reoperation, blinding the participants would be meaningless. Therefore, from the perspective of protecting participants’ rights, participant blinding will not be implemented either.

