## Statistical methods

### Statistical methods for primary and secondary outcomes {20a}

A statistician blinded to the treatment assignments will perform the analysis. For the primary endpoint, we will adhere to the intention-to-treat (ITT) principle; all patients who have been randomized and underwent surgery will be analyzed according to the group they were allocated to, irrespective of the treatment they received. When outcomes are missing for these patients, they will be treated as not having met the criteria for reoperation. The comparison for this endpoint between the two groups will be made using Fisher’s exact test. As a secondary analysis, the odds ratio estimates and their 95% confidence intervals will be calculated for the primary endpoint and secondary endpoints of the proportion of reoperations, the proportion of deaths, and the proportion of surgery-related complications. For the secondary endpoints of mRS, change in GCS, time from surgery to discharge, and operative time, the two groups will be compared by calculating the mean difference between the groups and its 95% confidence interval. 95% confidence intervals will be calculated using the Clopper-Pearson and bootstrap methods, respectively.

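### Section {11b} ties a requested change of procedure to leaving the trial, and sections {11b} and {20a} then give an operated switcher two incompatible fates, neither a true as-allocated analysis

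*Protocol article*

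**What the plan says.** All references are to the protocol article.

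- **Section {11b}, change of procedure.** After randomization, "patients who wish to change their assigned surgical procedure can request an intervention change and withdraw from the trial".
- **Section {11b}, non-assigned treatment.** If the surgeon gives a treatment other than the one assigned, intentionally or not, "the case will be excluded from the analysis, and crossover of participants is not permitted".
- **Section {20a}, analysis set.** For the primary endpoint, "all patients who have been randomized and underwent surgery will be analyzed according to the group they were allocated to", whatever treatment they received.
- **Section {20a}, missing outcomes.** "When outcomes are missing for these patients, they will be treated as not having met the criteria for reoperation".
- **Section {20a}, test.** "The comparison for this endpoint between the two groups will be made using Fisher’s exact test".
- **Section {16b}, timing of allocation.** "This process will be performed before surgery, and no registrations will be accepted thereafter".
- **Section {17a}, blinding.** Staff cannot be blinded, and "participant blinding will not be implemented either".
- **Section {18b}, retention.** Patients who miss visits are contacted, and the 6-month status is checked by telephone if they cannot attend. Patients who have withdrawn are not mentioned.

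**The concern.** Declining the allocated procedure and declining follow-up are separate decisions. Section {11b} joins them and leaves no stated route for a patient who makes only the first. Suppose a patient allocated to no irrigation learns the allocation before surgery, asks for irrigation, and is operated on that way. If withdrawal ends data collection, the 6-month outcome is missing because of the trial's own rule, and the reason for its absence is preference for one arm.

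Under section {20a} that missing value counts as a favourable result for the arm the patient refused. Under the exclusion sentence in section {11b} the patient disappears from the analysis instead. Either way, the as-allocated analysis that section {20a} promises is not delivered for this patient. The planned difference is only 5 percentage points, so losses concentrated in one arm could matter. An analysis plan written later can choose between exclusion and imputation, but it cannot recover outcomes that were never collected.

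**Working it through.** **1. What happens to one switcher.** Take a patient who is randomized, asks for the other procedure, and is operated on that way.

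- Under section {11b}, the surgeon has intentionally given a treatment other than the one assigned, so the case is excluded.
- Under section {20a}, the patient was randomized and operated on, so the patient stays in the allocated arm. If the 6-month outcome was not collected, it is scored as a non-event.
- A patient who withdraws and has no surgery is outside the section {20a} set, so the point does not apply to that patient.

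**2. The plan's own sample size.** Inputs from section {14}: 12% and 7%, α = 0.05 (taken as two-sided), β = 0.20, 10% dropout. The mean proportion is 9.5%.

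n = [1.960·√(2 × 0.095 × 0.905) + 0.842·√(0.12 × 0.88 + 0.07 × 0.93)]² / 0.05² = 538.7, so 539 per arm.

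539 × 1.10 = 592.9, so 593 per arm and 1186 in total. The stated figure is reproduced.

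**3. Assumptions for the illustration.** The protocol gives no switching share, so 0 to 10% of an arm is assumed. Rejection rates are exact, by enumeration, for a two-sided 5% Fisher test with 593 per arm; the article does not state the sidedness. For a share w of an arm with event proportion p:

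- Scored as non-events: p × (1 − w).
- Followed up and analysed as allocated: p × (1 − w) + r × w, where r is the risk of the procedure received (assumed 7% with irrigation, 12% without).

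**4. Bias when there is no true effect.** Switchers in one arm only are scored as non-events.

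| True proportion, both arms | No switchers | 5% of one arm | 10% of one arm |
|---|---|---|---|
| 12% | 4.1% | 5.1% | 8.4% |
| 7% | 3.9% | 4.4% | 6.1% |

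At 12% the scored proportions are 12% × 0.95 = 11.4% and 12% × 0.90 = 10.8%. If both arms lose 10%, the rejection rate stays at 4.0%. The harm therefore comes from unequal loss.

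**5. When 12% v 7% is true.** Without switching, power is 81.6%.

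| Switchers | Scored as non-events | Power | Followed up | Power |
|---|---|---|---|---|
| 1% of non-irrigation | 11.88% v 7% | 79.9% | 11.95% v 7% | 80.9% |
| 5% of non-irrigation | 11.4% v 7% | 71.8% | 11.75% v 7% | 77.8% |
| 10% of non-irrigation | 10.8% v 7% | 59.7% | 11.5% v 7% | 73.6% |
| 10% of irrigation | 12% v 6.3% | 91.7% | 12% v 7.5% | 71.6% |
| 10% of both arms | 10.8% v 6.3% | 76.7% | 11.5% v 7.5% | 61.8% |

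The scored difference moves from 5.0 points to 3.8 (10.8 − 7.0) or to 5.7 (12.0 − 6.3), depending on which arm loses patients. In the last two rows follow-up gives lower power than scoring as non-events. The higher power there comes from the scoring rule and is not information about the treatment.

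**The case against.** The strongest reply is that the article does not settle what happens to a switcher. A reader might infer that the patient must leave, that follow-up stops, and that the patient certainly stays in the intention-to-treat set as a success. The documents do not support this as fact:

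- Section {11b} says that patients can request a change and withdraw. No section says that data collection ends. That it does is a reasonable inference, since crossover is barred and no follow-up after withdrawal is described, but it remains an inference.
- The exclusion sentence in section {11b} is not limited to deviations the patient did not ask for, so it also fits a requested switch. Retention with a favourable score is only one of two readings.

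A reader might also infer that switchers escape the non-adherence count in section {21a}. That is speculative. Section {11c} requires sites to report whether the assigned treatment was done, and section {21a} compares allocation with the irrigation data.

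Frequency may be low: under sections {26a} and {16c} patients consent to surgery and to research before they are randomized. It would also be wrong to charge the whole fall in power from 81.6% to 71.8% at 5% switching to this rule. Part of it is dilution from switching, which follow-up does not remove. The rule's own share is 77.8% to 71.8%, about 6 points.

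These replies limit the certainty and the size of the point. They do not supply a route to switch and stay in follow-up, and they do not reconcile the two sections.

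**Conclusion.** The point holds as a defect in the stated rules. Section {11b} couples a requested change of procedure with withdrawal and gives no alternative. Sections {11b} and {20a} then assign the same operated patient to exclusion or to the allocated arm with a possible imputed non-event. In an open trial with allocation known before surgery, losses of this kind may be unequal and may favour either arm.

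The size cannot be known from the document. Under the assumed shares, loss from one arm only at a 12% event proportion raises the null rejection rate from 4.1% to 5.1% (5% of the arm) or 8.4% (10%). The 5% case is barely above the nominal level because Fisher's test starts below it, and equal losses leave the rate essentially unchanged. The argument rests on bias and not on power, since following switchers raises power in some scenarios and lowers it in others. It should be fixed, together with reconciling the exclusion rule in section {11b} with section {20a}.

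**What to change.** 1. Reword section {11b} so that a patient who declines or changes the allocated procedure remains in the trial. Record the procedure actually done and collect the 72-hour, 4–6-week and 6-month data already scheduled in section {13}.
2. Reserve withdrawal for a patient who refuses follow-up. Ask that patient separately whether routine records on reoperation and death may still be used.
3. State one fate for these patients in both {11b} and {20a}: analysed in the arm to which they were allocated. Remove or reconcile the exclusion sentence in the same amendment.
4. Say in section {21a} that a requested switch counts as a discrepancy between allocation and treatment.

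The cost is amendment wording, one REDCap item separating refusal of the procedure from refusal of follow-up, and a sentence in the consent form. No visits are added and the sample size does not change. Patients may still refuse follow-up. The downside is that non-adherence becomes more visible. The change is worth most while patients are still in follow-up, because outcomes not collected may not be recoverable.

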### Sample size {14}

The present study aimed to recruit 1186 cases, with 593 patients allocated to each group. The target number of cases was determined based on a previous meta-analysis that examined the efficacy of irrigation for CSDH. A meta-analysis reports a recurrence proportion of 8.06% (38/471) in the irrigation group and 13.05% (59/452) in the non-irrigation group; however, this difference was not statistically significant [17]. The 95% confidence intervals were 5.8–10.9% for the irrigation group and 10.1–16.5% for the non-irrigation group. To account for the differences in outcome measures between the prior and present studies, we set the proportions of patients meeting the criteria for ipsilateral reoperation at 7% for the irrigation group and 12% for the non-irrigation group. Using *α* = 0.05 and *β* = 0.20 and accounting for a 10% dropout proportion, a total of 1186 cases, with 593 cases in each group, have been calculated to be necessary for the current study. In determining the sample size, the sample size calculation tool for 2 × 2 contingency tables by Kazuhiko Nagashima was used [35] (https://nshi.jp/contents/js/twofreq/).

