### Composition of the data monitoring committee and its role and reporting structure {21a}

A monitor authorized by the Nagoya University School of Medicine will supervise the sources of consent forms and clinical data collected at each facility. Case registration will be temporarily suspended if the number of cases confirmed by monitoring shows discrepancies between the assigned treatment group and the irrigation information collected by REDCap® exceeds 5% of the target number of cases for this trial (59 cases). Subsequently, an independent monitoring committee consisting of three external experts who are not affiliated with this study will be consulted for advice on the feasibility of continuing this trial as well as on measures to prevent noncompliance with the assigned treatment group if the trial is to be continued. The independent monitoring committee has the following three members: [name], Department of Neurosurgery, Aichi Medical University Graduate School of Medicine, Nagakute, Aichi, Japan; [name], Department of Neurosurgery, Nagoya Central Hospital; and [name], Department of Neurosurgery, Aichi Cancer Center Hospital, Nagoya, Japan.

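### Patients given the non-assigned procedure are excluded from the analysis in section 11b but kept as allocated in section 20a, so the primary analysis set is contradictory

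*Protocol article*

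**What the plan says.** Two sections of the protocol article deal with a patient who was randomised, had surgery, and received the other group's procedure.

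- **Section 11b (discontinuing or modifying allocated interventions).** If the surgeon "administers a treatment different from the assigned group after randomization, the case will be excluded from the analysis". The sentence covers intentional and unintentional deviations alike and adds that "crossover of participants is not permitted". It does not say which analysis is meant.
- **Section 20a (statistical methods).** The primary endpoint follows intention-to-treat: "all patients who have been randomized and underwent surgery will be analyzed according to the group they were allocated to", and this holds "irrespective of the treatment they received".

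Three other places bear on the point. Section 11c has investigators report whether the assigned treatment was performed, together with details of the irrigation fluid, so the treatment given is known for each case. Section 21a suspends registration once confirmed mismatches between assignment and irrigation data exceed 59, which is 5% of 1186. Section 20c is headed as covering protocol nonadherence, but its text deals only with missing data.

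**The concern.** Read literally, the same patient is both outside and inside the primary analysis. The two rules also differ in validity. Section 20a keeps the groups as randomisation formed them, among operated patients. Section 11b removes patients because of something that happened after randomisation, at the hands of a surgeon who knows the allocation and may have deviated on purpose. If deviations are prompted by what is found at operation, the removed patients may differ in recurrence risk from those who remain, and they may come mainly from one arm. The comparison would then no longer be the randomised one.

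The trial is unblinded, and the protocol promises its analysis plan only before data lock. A choice between the two rules should not be left until outcomes by arm are already visible to those running the trial.

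**Working it through.** **1. The texts side by side.** Take a patient randomised to no irrigation, operated on, and irrigated.

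| Section | Is the patient in the analysis? | In which group? |
|---|---|---|
| 11b | No | – |
| 20a | Yes | No irrigation, as allocated |

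A per-protocol set to which 11b might refer would reconcile the two, but the article names none. The conflict needs no arithmetic. The steps below only show what could hang on it.

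**2. The plan's own figure.** The inputs in section 14 are event proportions "at 7% for the irrigation group and 12% for the non-irrigation group", alpha 0.05 (two-sided assumed), power 80% and 10% dropout. With pooled variance and no continuity correction,

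n = [1.96·√(2·0.095·0.905) + 0.842·√(0.12·0.88 + 0.07·0.93)]² / 0.05² ≈ 539 per arm.

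539 × 1.10 = 592.9, so 593 per arm and 1186 in total. The stated size reproduces and is not in question.

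**3. False rejection if exclusion is selective.** *Assumed:* true risk 12% in both arms; k patients with risk 25% excluded. The documents give neither k nor the 25%. The remaining rate in an arm is

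(0.12 × 593 − k × 0.25) / (593 − k).

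- k = 30: (71.16 − 7.50)/563 = 11.31%
- k = 59: (71.16 − 14.75)/534 = 10.56%

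Two-sided Fisher rejection by full enumeration:

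| Exclusions | Rejection |
|---|---|
| None | 4.1% |
| 30, one arm only | 5.9% |
| 59, one arm only | 10.7% |
| 59, split 30/29 across arms | 4.5% |

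If the excluded patients have average risk (12%), both arms stay at 12% and rejection stays below the nominal 5%.

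**4. Power under the two rules, like for like.** *Assumed:* irrigation arm 7%; k control patients are irrigated and so receive the planned relative risk of 7/12; r is their risk without irrigation. The control rate is

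- excluded: (71.16 − k·r)/(593 − k)
- as allocated: (71.16 − k·r + k·r·7/12)/593

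| k, r | Control rate as allocated | Control rate excluded | Power as allocated | Power excluded |
|---|---|---|---|---|
| 59, 25% | 10.96% | 10.56% | 63% | 55% |
| 30, 25% | 11.47% | 11.31% | 73% | 70% |
| 59, 12% | 11.50% | 12.00% | 74% | 81% |

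With no crossover at all, Fisher power is 81.6%. The two rules give different power in every row, and the order reverses when crossover is unrelated to risk.

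**The case against.** The strongest reply is that section 20a already settles the matter. It is the statistical section, it is specific to the primary endpoint, and it states the correct rule in plain terms. Section 11b belongs to the description of the interventions and speaks loosely of an analysis. It might have been meant for analyses other than the primary one, and a registered analysis plan is promised before data lock. Much of this stands: most statisticians would follow 20a. But 11b carries no such limit, and two incompatible rules already in the protocol are not a detail left for later.

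A reader might go further in three ways that the documents do not support.

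- **That the rule costs about 27 points of power, from 82% to 55%.** The 82% assumes no crossover at all. In the same scenario the as-allocated analysis has 63%, so most of the loss comes from crossover itself and would remain after the fix.
- **That false rejection would be near 11%.** This needs all 59 mismatches in one arm, at about twice the average risk. The 59 in section 21a counts both arms together, and nothing in the article suggests one-sided deviation or a 25% risk.
- **That the suspension threshold in section 21a is part of the error.** It is clearly defined and can be operated. Whether to use a fixed count or a running rate is a monitoring preference that neither causes nor cures the contradiction. The sentence in 11b on patients who ask to change procedure and withdraw is likewise a separate consent question.

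**Conclusion.** The contradiction is established from the text alone: 11b and 20a cannot both be applied to an operated patient who received the other procedure. It should be corrected, because the exclusion rule conflicts with the declared principle and can bias the randomised comparison.

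It does not follow that the trial's result will be biased, or that two analysts would necessarily report different results. The number of such cases, their risk and their distribution over the arms are not in the documents, so the size and direction of any bias are unknown. Under the assumed inputs, the effect on false rejection ranges from none to a rise from 4.1% to 10.7%, the latter at a deliberately extreme corner. Power under exclusion may be lower or higher than under analysis as allocated. The case for analysis as allocated therefore rests on validity, not on power.

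**What to change.** Delete the exclusion clause from section 11b and put in its place a statement such as: *A patient who receives the other group's procedure stays in the primary analysis in the group assigned by randomisation (see section 20a).* The conduct rule on crossover in the same sentence need not change. If the investigators want to see the result without these patients, they should define a per-protocol set by name and report it as a sensitivity analysis only. The analysis plan should use the same wording.

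The cost is a one-sentence amendment. No further data are needed, since section 11c already collects the treatment given. The small downside is that when crossover is unrelated to risk, analysis as allocated has less power than exclusion (74% against 81% in the third row of the power table).
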